### Sample size

2.9

The data for DL in this study will be a matched series of spinal axial CT and sagittal MRI so that each participant represents one sample. According to a sample size determination study based on DL models and 3D images, the receiver operating characteristic (ROC) curve of classification accuracy became stable when the training sample size increased to 200, and reached a high 98% classification accuracy at a training sample size of 1,000 per class (27). In the present study, binary predictions are warranted for each subgroup of BCL, so at least 250 participants in the internal dataset, containing 200 (80%) for the training set, as the minimal sample size will be acceptable for accurately performing the task. However, more eligible patients up to 1,250 participants, containing 1,000 (80%) for the training set, will be enrolled to achieve a higher accuracy.

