A primary concern of spine surgeons during PKP is reducing the occurrence of BCL. Despite rigorous efforts, the rate of BCL remains alarmingly high, even up to 80% (9, 10). This is particularly disturbing as certain types of leakage can cause severe complications, even mortality. Notably, leakage remains an unavoidable risk even if the operator is an experienced specialist. Currently, intraoperative C-arm fluoroscopy is still the most predominant approach for monitoring BCL, yet its image quality is even inferior to that of plain radiographic images (23). This hampers the early and accurate detection of BCL, particularly leakage into the spinal canal, during the intervention. Consequently, developing an effective and reliable preoperative BCL prediction model to facilitate precise individualized risk prediction in patients with OVCF is crucial. To date, only a few studies attempted to predict BCL using several traditional ML models (16–18). Li et al. used six ML models to predict BCL by incorporating clinical baseline characteristics and surgery-related variables, and the AUROC for these models was 0.633–0.898 (16). Further, Hu et al. incorporated radiographic variables from 425 patients to predict BCL using five ML models and revealed that the XGBoost demonstrated the highest AUROC of 0.8819 (17). However, these traditional ML models had inherent limitations, such as depending on manually extracted features and a lack of subtyping for BCL, which restricted their generalization. Recently, an initial attempt has been made to predict BCL using a DL model, but it still relied on manual image feature extraction (17). In addition, the predictive performance of this DL model was inferior than that of the XGBoost model. This indicates that while DL has notable advantages in several domains like image, language, and audio processing, tree-based ML methods have achieved robust predictions more easily than DL for small-scale data (17). However, with the rapid advancements in artificial intelligence technology, it is currently attractive and of great potentiality in developing more accurate and concise DL models by large datasets for predicting BCL.

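### Section 2.9 turns a benchmark of 1,000 training samples per class into a total of 1,000, so the benchmark does not support the upper sample size

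*Protocol article*

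**What the plan says.** Section 2.9 draws two points from one cited study of deep learning on 3D images. The ROC curve of classification accuracy "became stable when the training sample size increased to 200", and the model "reached a high 98% classification accuracy at a training sample size of 1,000 per class". The section takes the patient as the unit ("each participant represents one sample") and describes the task as two-class ("binary predictions are warranted for each subgroup of BCL").

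From this it derives two sizes for the internal dataset:

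- A minimum: "so at least 250 participants in the internal dataset, containing 200 (80%) for the training set, as the minimal sample size will be acceptable".
- An upper figure of 1,250 participants, "containing 1,000 (80%) for the training set, will be enrolled to achieve a higher accuracy".

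The words per class are attached to the 1,000 in the benchmark. They do not reappear in either target. Section 2.5 separately divides the retrospective internal dataset 9:1 into training and validation sets, which is a different training share from the 80% in 2.9.

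**The concern.** A benchmark per class and a total over classes are different quantities. If the cited accuracy was seen with 1,000 samples in each class, a total of 1,000 over two classes is at most half the benchmark. It is a smaller fraction for any subtype found in fewer than half of patients. For an uncommon subtype, the number of patients with that leakage governs what the model can learn, more than the number of patients enrolled.

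The point matters because this benchmark is the only quantitative support offered for either size. Section 2.8 makes sensitivity, specificity and AUROC for each subtype the primary outcomes, and the Discussion (section 3) makes recall for spinal canal leakage a central goal. A reader of 2.9 would believe that the sample had been matched to a published learning curve for these tasks. At the upper size it has not.

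**Working it through.** **Inputs**

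- Benchmarks: 200 (class basis not stated) and 1,000 per class (section 2.9).
- Unit: one patient is one sample (2.9).
- Classes per task: two, leak or no leak, for each of four subtypes (2.9; subtypes defined in 2.6).
- Training share: 80% (2.9) or 90% (9:1 split, 2.5).
- Subtype prevalence p: not given. The Introduction gives only 5–80% for leakage of any kind. The values 50%, 20%, 10% and 5% below are assumptions; 50% is the most favourable possible.

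**Step 1. Reproduce the plan's figures.** Internal N = training size / training share.

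- 200 / 0.80 = 250 and 1,000 / 0.80 = 1,250. Both match exactly.
- With the 9:1 split: 200 / 0.90 = 223 and 1,000 / 0.90 = 1,112 (rounded up). Neither matches.

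So 250 and 1,250 come out only if 200 and 1,000 are total training patients.

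**Step 2. Training patients needed for 1,000 per class.** The smaller class is a fraction min(p, 1 − p) of the training set, so the total needed is 1,000 / min(p, 1 − p).

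**Step 3. What the planned training sets contain.** Smaller class = training size × min(p, 1 − p).

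| Assumed prevalence | Training total for 1,000 per class | Internal N at 80% | Smaller class in 1,000 | Smaller class in 200 |
|---|---|---|---|---|
| 50% | 2,000 | 2,500 | 500 | 100 |
| 20% | 5,000 | 6,250 | 200 | 40 |
| 10% | 10,000 | 12,500 | 100 | 20 |
| 5% | 20,000 | 25,000 | 50 | 10 |

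**Step 4. Does the other split help?** Under 9:1, 1,250 × 0.90 = 1,125 training patients. That is still below 2,000, and the smaller class is at most 1,125 × 0.5 = 562.5, so 562.

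**Step 5. The minimum of 200.** If the 200 were also per class, 200 / 0.5 = 400 training patients would be needed at 50% prevalence, and 1,000, 2,000 or 4,000 at 20%, 10% or 5%. The text does not settle whether it is, so these figures are conditional. What holds on either reading is that the smaller class in 200 patients is at most 100.

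**The case against.** The strongest reply is that the plan makes no numerical promise. It links the larger training set only to better accuracy, never to 98%. A learning curve from another task cannot show what 1,000 patients will or will not achieve here. That stands. A reader might infer that neither 200 nor 1,000 can deliver the intended performance, but the documents do not support so strong a claim. They show only that the cited benchmark does not justify the 1,000.

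One could also argue that the same patients serve all four subtype tasks, so no multiplication by subtype is needed. That is right, but each task still has two classes, and the shortfall follows from those two alone.

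Three further inferences are tempting and do not hold:

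- *The 200 was mis-scaled in the same way.* The words per class follow only the 1,000, and the cited study is not at hand. The same slip is possible but not shown.
- *The Discussion shows that 200 is too few.* It reports a deep learning model that did worse than XGBoost and remarks that "tree-based ML methods have achieved robust predictions more easily than DL for small-scale data". That model relied on manually extracted image features, whereas the planned model takes the images directly. The comparison does not establish that 200 is inadequate.
- *Spinal canal leakage will yield only a handful of test events.* No subtype prevalence is given, and nothing says that this type is the rarest. Projecting the size of the prospective test set would also require constant accrual, and a reading of 250 and 1,250 as retrospective patients only.

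Finally, a condensed article may leave test-set precision to a fuller document. Its absence is not counted as a fault here. It enters only as part of a sound replacement for the benchmark.

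**Conclusion.** The concern holds for the upper figure. A per-class benchmark is used as a total, and no prevalence makes 1,000 patients in total equal to 1,000 per class. The shortfall is a factor of at least two (2,000 against 1,000), and 5, 10 or 20 at assumed subtype prevalences of 20%, 10% or 5%. The factor of two needs no assumption about prevalence; the larger factors do. The training share does not rescue it, since 1,125 is also below 2,000.

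For the minimum of 200, the conclusion is narrower: class balance is ignored and the smaller class is at most 100.

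The plan's division and multiplication are correct; the fault lies in how the benchmark is applied. The datasets are consecutive patients in fixed calendar windows (section 2.2), and no stated outcome or analysis is invalidated. This should be fixed, because the stated basis of the upper sample size is wrong and restating it is cheap.

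**What to change.** Revise section 2.9, without enrolling more patients:

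1. Remove the 98% per-class benchmark as support for 1,000 training patients in total.
2. Do not call 200 training patients sufficient for accurate prediction without regard to class balance.
3. Restate the size as the expected number of leak and non-leak cases for each subtype, in the training set and in each test set, using the centres' own leak rates.
4. Give the precision of sensitivity and AUROC that follows for the rarest subtype.
5. Keep the prospective internal and external results separate, as section 2.8 reports performance in both internal and external test sets. Pooling them to gain events would blur that distinction.
6. In the same edit, reconcile the 80% training share in 2.9 with the 9:1 split in 2.5, since the expected counts depend on it.

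The cost is protocol wording and a tabulation of leak rates at the two centres. The downside is that the stated adequacy of the sample becomes less favourable.

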### Statistical analysis

2.10

All data will be analyzed using *Python* 3.8.0. The confusion matrix of DL model and readers in detecting Type I–IV of BCL will be used to evaluate the predicting performance. Quantitative evaluation metrics containing accuracy, sensitivity, specificity, precision, and F1 score, will be calculated based on the confusion matrices. Meanwhile, the ROC curve for binary classification will be plotted and AUROC will be calculated. Linearly weighted Cohen’s kappa coefficient between Reader 3, Reader 4, and the DL model with the reference standard will be used to assess the interobserver and model’s reliability. Statistical significance is set at *p* < 0.05.

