### Diagnostic criteria for BCL and dataset labeling

2.6

Although postoperative CT is the most accurate approach to detect BCL, it is not necessary for all types of BCL (22), and the postoperative X-ray can achieve satisfactory sensitivity (23). Therefore, either the immediate postoperative spine CT or X-ray will be checked to confirm the occurrence of BCL. BCL was defined as the presence of extravertebral cement. Further, we proposed modified four subtypes of BCL are differentiated by the location of the extravertebral cement according to Bermejo et al. (9): (1) Type I, leaking through the segmental vein; (2) Type II, leaking through the cortical defect to perivertebral soft tissue; (3) Type III, leaking into intervertebral disk; (4) Type IV, leaking into the spinal canal (through basivertebral vein or cortical defect) (Figure 2).

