### Outcomes

2.8

The primary outcome measures will be the main exactitude performance of DL model for binary predicting (0/1) different subtypes of BCL, including sensitivity, specificity, and the area under the receiver operating characteristic curve (AUROC), in both internal and external test sets. Secondary outcomes include other exactitude performance such as accuracy, precision, and F1 score. Additionally, the reliability of the model will be evaluated by calculating its consistency with reference standards and comparing it with that of clinician prediction.

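### Linearly weighted kappa is specified for leak types that have no order: on one Type I–IV variable it depends on the numbering, on 0/1 calls the weighting does nothing (should-fix)

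*Protocol article*

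**What the plan says.** Section 2.10 (Statistical analysis) names one agreement statistic: "Linearly weighted Cohen’s kappa coefficient between Reader 3, Reader 4, and the DL model with the reference standard", which "will be used to assess the interobserver and model’s reliability". It gives no other weights and no reason for linear ones.

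Section 2.6 (Diagnostic criteria for BCL and dataset labeling) says that the four subtypes "are differentiated by the location of the extravertebral cement": segmental vein (I), perivertebral soft tissue (II), intervertebral disk (III) and spinal canal (IV). No rank is attached to the numbers.

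On the form of the prediction, section 2.8 (Outcomes) speaks of "binary predicting (0/1) different subtypes of BCL", and section 2.9 (Sample size) says that "binary predictions are warranted for each subgroup of BCL". Section 2.10 also refers to "The confusion matrix of DL model and readers in detecting Type I–IV of BCL", without saying whether this is one table with a row per type or a separate 2×2 table for each type.

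Section 2.8 lists sensitivity, specificity and AUROC as primary. Agreement with the reference standard, compared with that of clinicians, is added after the primary and secondary measures.

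**The concern.** A linear weight gives partial credit according to the distance between category numbers. That is meaningful for a graded scale. For locations it means that calling a canal leak (IV) a disk leak (III) is penalised one third as much as calling it a segmental vein leak (I), only because of the labels.

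Reading the numbers as a severity scale does not rescue the choice. The Discussion places canal leakage among the most severe types, but it does not rank Types I to III. The Introduction says that leakage into the paravertebral vein can be fatal, and the Discussion links such leakage, basivertebral leakage excluded, to pulmonary cement embolism. In this scheme that corresponds to Type I, the end of the numbering furthest from IV.

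At stake is the comparison of the model with Readers 3 and 4, which the Discussion presents as a strength of the study. On a multi-category table, the size of each kappa, and possibly the order of model and readers, could reflect label numbers rather than agreement.

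**Working it through.** The article states no kappa value, so there is no figure to reproduce. All cell counts below are assumptions; the article gives none.

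**Formula.** κ = 1 − Σ(w × observed proportion) / Σ(w × proportion expected from the margins). Linear weights are w = |i − j|/(k − 1). Unweighted kappa uses w = 1 for every off-diagonal cell.

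**1. The 0/1 calls (k = 2).** Here w = |i − j|/1, which is 0 on the diagonal and 1 off it. These are the unweighted weights, so the two coefficients are identical. Over 2,000 random 2×2 tables the largest difference was 0.

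**2. One Type I–IV variable (k = 4).** Take 20 reference cases per type (n = 80), all correct except 10 of the 20 Type IV cases. Each row margin is 0.25. The mean distance from columns I, II, III and IV to the four rows is 1.5, 1, 1 and 1.5.

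- *Ten Type IV cases called III.* Column margins are 0.25, 0.25, 0.375, 0.125. Observed: (10/80) × 1/3 = 0.0417. Expected: (0.25 × 1.5 + 0.25 × 1 + 0.375 × 1 + 0.125 × 1.5)/3 = 1.1875/3 = 0.3958. κ = 1 − 0.0417/0.3958 = 0.895.
- *Ten Type IV cases called I.* Column margins are 0.375, 0.25, 0.25, 0.125. Observed: (10/80) × 1 = 0.125. Expected: (0.375 × 1.5 + 0.25 × 1 + 0.25 × 1 + 0.125 × 1.5)/3 = 1.25/3 = 0.4167. κ = 1 − 0.125/0.4167 = 0.700.
- *Unweighted, both cases.* (70/80 − 0.25)/(1 − 0.25) = 0.833.

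**3. Can the order of two raters reverse?** Let a second rater misclassify only 5 of the 20 Type IV cases, all as Type I. Observed: 5/80 = 0.0625. Expected: (0.3125 × 1.5 + 0.25 + 0.25 + 0.1875 × 1.5)/3 = 0.4167. Linear κ = 0.850, below the 0.895 of the rater who misclassified ten as Type III. Unweighted, the order is the other way: (75/80 − 0.25)/0.75 = 0.917 against 0.833.

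**4. Same errors, different pair of types.** With 30 cases per type (n = 120) and 20 errors split evenly in both directions between two types:

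| Types confused | Linear κ | Unweighted κ |
|---|---|---|
| I and II | 0.867 | 0.778 |
| I and III | 0.733 | 0.778 |
| I and IV | 0.600 | 0.778 |

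**5. Same table, different numbering.** For a 137-case table with rows (30, 2, 2, 8), (3, 20, 2, 2), (2, 2, 35, 2) and (7, 2, 2, 16), linear κ is 0.567 as numbered. It ranges from 0.553 to 0.712 over the 24 ways of numbering the types. Unweighted κ is 0.644 under all of them.

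**The case against.** The strongest reply is that the harmful reading is the less likely one. Sections 2.8 and 2.9 describe binary predictions for each subtype, and section 2.10 plots ROC curves for binary classification. On 2×2 tables the linear weight changes nothing. This stands, and it lowers the severity. It does not remove the point, because section 2.10 leaves the table open and the words it uses have an effect only on a multi-category table.

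A reader might infer that the kappa could hide errors on Type IV. The documents do not support that. Sensitivity, specificity and AUROC for the subtypes are primary, and section 2.10 derives sensitivity, specificity, precision and F1 from confusion matrices for the model and the readers. Missed canal leaks would show there, whatever the kappa.

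A reader might also argue that a single kappa forces one type on cases that leak at several sites. The article nowhere says that a case can have several leak types, nor gives this as the reason for the binary outputs. The point does not need that premise.

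Finally, the sizes above come from assumed tables. That is right: they show that numbering can matter, not how much it would matter in these data.

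**Conclusion.** The point holds as a should-fix. Linear weights have no stated basis for Types I–IV. On one multi-category variable the coefficient depends on arbitrary numbering: 0.89 against 0.70 for the same number of Type IV errors, and a possible reversal of two raters, under the assumed counts. On the 0/1 calls the weighting has no effect, and the statistic is merely misnamed.

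That numbering affects a multi-category linear kappa follows from the formula; only the size of the effect rests on assumptions. A reader might conclude that the model's main evaluation is compromised. It is not: no primary measure uses kappa, and no sample size or decision rule in the article is tied to it. The statistic is, however, fixed in the article's text, so this is not a detail left to a fuller plan.

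**What to change.** In section 2.10, replace the linearly weighted coefficient with unweighted Cohen's kappa, computed separately for each subtype's 0/1 call, for Reader 3, Reader 4 and the model against the reference standard. If a single multi-category variable is intended, say so and use unweighted nominal kappa.

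The cost is one phrase in the text and trivial programming; no new data are needed. Confidence intervals and positive and negative agreement beside each kappa would be useful but optional, and their absence from the article is not an error.

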### Dissemination

2.11

The findings of the study will be published in peer-reviewed journals, and national or international conferences. All data related to this study will be kept until 5 years of publication, and available from the corresponding author on reasonable request.

## Discussion

3

This study aims to develop and validate a DL-based multimodal image analysis model capable of predicting subtypes of BCL using preoperative spine CT and MRI scans of patients with OVCF. The model holds an imperative clinical significance. By preoperatively identifying patients at high risk for each subtype of BCL, clinicians can formulate more targeted treatment strategies to minimize the incidence of BCL thus improve clinical outcomes. Moreover, the model will promote information sharing and decision-making between clinicians and patients efficiently, thereby increasing the overall quality of healthcare services.

A primary concern of spine surgeons during PKP is reducing the occurrence of BCL. Despite rigorous efforts, the rate of BCL remains alarmingly high, even up to 80% (9, 10). This is particularly disturbing as certain types of leakage can cause severe complications, even mortality. Notably, leakage remains an unavoidable risk even if the operator is an experienced specialist. Currently, intraoperative C-arm fluoroscopy is still the most predominant approach for monitoring BCL, yet its image quality is even inferior to that of plain radiographic images (23). This hampers the early and accurate detection of BCL, particularly leakage into the spinal canal, during the intervention. Consequently, developing an effective and reliable preoperative BCL prediction model to facilitate precise individualized risk prediction in patients with OVCF is crucial. To date, only a few studies attempted to predict BCL using several traditional ML models (16–18). Li et al. used six ML models to predict BCL by incorporating clinical baseline characteristics and surgery-related variables, and the AUROC for these models was 0.633–0.898 (16). Further, Hu et al. incorporated radiographic variables from 425 patients to predict BCL using five ML models and revealed that the XGBoost demonstrated the highest AUROC of 0.8819 (17). However, these traditional ML models had inherent limitations, such as depending on manually extracted features and a lack of subtyping for BCL, which restricted their generalization. Recently, an initial attempt has been made to predict BCL using a DL model, but it still relied on manual image feature extraction (17). In addition, the predictive performance of this DL model was inferior than that of the XGBoost model. This indicates that while DL has notable advantages in several domains like image, language, and audio processing, tree-based ML methods have achieved robust predictions more easily than DL for small-scale data (17). However, with the rapid advancements in artificial intelligence technology, it is currently attractive and of great potentiality in developing more accurate and concise DL models by large datasets for predicting BCL.

Notably, different types of BCL result in various secondary complications. However, there is a lack of studies elaborating subtype analysis for BCL, which is one of the chief culprits resulting in the gaps between existing prediction models and real clinical applications. Drawing on the work of Bermejo et al. (9), we propose a modified BCL classification system (types I–IV) based on the location of extra-vertebral bone cement. In Bermejo’s system, basivertebral vein leakage is bracketed in Type S together with segmental vein leakage, and spinal canal leakage is bracketed in Type C together with leakage through cortical defect to elsewhere. However, from a prognosis point of view, basivertebral vein leakage may delay neurological complications despite it is generally safer than through cortical defect. Furthermore, paravertebral vein leakage (excluding basivertebral vein leakage), has been proven as an independent risk factor for pulmonary cement embolism. Therefore, it is reasonable to divide basivertebral vein leakage into spinal canal leakage, as a serious situation to avoid as much as possible. Similarly, Shi et al. developed a nomogram to predict intra-spinal canal leakage, a type same as Type IV in this study, which combined leakage through basivertebral vein with cortical defect (24). Leaking into the spinal canal is among the most severe types of leakage, potentially causing subsequent nerve compression and even disability (28). Consequently, a crucial goal of this modified classification system is to maximize the recall of the DL model on the premise of the overall accuracy, thereby minimizing the risk of mispredictions for spinal canal leakage. This modified classification system is expected to make more accurate preoperative predictions for BCL, providing further targeted clinical guidance and satisfied outcomes.

Overall, our study presents several significant advantages over previous predictive models. First, our model directly uses preoperative CT and MRI images as inputs. Previous studies have emphasized the clinical significance of radiology-related variables such as cortical destruction, intervertebral cleft, bone mineral density, fracture severity, fracture type, and basivertebral foramen sign in BCL prediction (9, 17, 29–31). In particular, Hu et al. determined only preoperative imaging parameters and intraoperative cement volume as independent risk factors for BCL after analyzing over 20 potential risk factors, including baseline characteristics, medical history-, surgery-, and radiology-related variables (17). Hence, a purely image-based DL prediction model is both adequate and reasonable. The DL model adaptively learns feature information from preoperative images without manual intervention, which enables seamless integration into current clinical workflows (32). Second, BCL is an immediate intraoperative complication without being affected by various confounding factors during long-term follow-up, improving the credibility and interpretability of our predictive model. Third, our model not only predicts the occurrence of BCL during PKP, but also enables further subtypes of leakage. Such predictive results are instrumental for clinicians in developing more thorough and personalized treatment plans. Next, our models will be trained on relatively large sample size datasets and validated with prospective, multi-center datasets, which not only improves the performance of the model, but also improves its generalization and applicability across different healthcare settings. Moreover, we will compare the prediction capability of our model with that of clinicians to test its reliability to further evaluate the performance of the model, which will provide a more comprehensive and objective evaluation of the model’s performance.

This study has several limitations. First, the training set for the model is derived from a single-center retrospective dataset, which may introduce selection and subjective bias. Future research should use larger, prospective, and multicenter datasets to train and validate the model, thereby improving its reliability and generalizability. Second, our study solely used preoperative medical imaging data as input, omitting surgery-related variables such as surgical access, puncture pin location, and cement volume, which have been proven to be associated with BCL (9, 17, 29, 31, 33, 34). However, our model is designed to serve as a preoperative prediction tool, to conduct straightforwardly and easily personalized preoperative risk assessment and surgical planning. Finally, as the gold standard for BCL assessment remains postoperative CT examination; thus, not all patients in this study underwent postoperative CT, which may somehow result in inaccuracy of the assessment of BCL.

In conclusion, we will develop a multimodal image analysis model based on DL algorithms for predicting intraoperative BCL in PKP. To the best of our knowledge, it will be the first study to directly utilize preoperative CT and MRI images for BCL subtype prediction. Although there are numerous challenges and unresolved issues in the successful development and application of this model, its potential is highly promising. This approach facilitates individualized and intelligent preoperative assessments for patients with OVCF, providing a crucial basis for surgical decision-making. In particular, the model can be extended and applied in remote areas where medical resources are relatively scarce, so that more patients can benefit from quality perioperative evaluation and management strategies. We will continue to explore the feasibility and limitations of this model in practical clinical applications in future studies, to further improve its accuracy and utility.
